### Quantitative Analysis

#### Adapted ABC questionnaire validation

The baseline data from the adapted ABC questionnaire will be used to explore properties such as item functioning, responsiveness, validity and reliability. Factor analysis and summary statistics will be used to determine internal consistency and item correspondence to constructs underlying the outcome measures.

#### Descriptive

Descriptive statistics of demographic variables (age, gender, ethnicity, marital group, access to health care, presence of comorbid conditions, socioeconomic indicators, i.e. educational attainment and occupational status) and outcomes for baseline and follow-up, split by treatment arm, will be presented to summarise the unadjusted data. The response rate will be similarly summarised. Assessment of drop-out bias will not be tested but will tabulate the baseline demographic descriptives of those completing and those not completing the 2 week follow-up.

#### Main analyses

The primary analysis will be on a complete case basis following intention-to-treat principles, and will determine the difference in ABC score between the two arms at 2 weeks, including baseline cancer symptom recognition as a covariate. The distributional assumptions of the linear model will be checked by visual inspection of fitted versus residuals plots. The primary outcome data will be transformed where appropriate. If they remain non-normal, bootstrapping will be used to generate regression coefficients and confidence intervals. The mean (SD) ABC for the control and intervention groups at baseline and follow-up will be tabulated. The primary outcome effect will be reported unadjusted and adjusted for baseline ABC, with 95% CI and *p*-value. Covariates to be considered for inclusion in the model are age, gender, recruitment setting and socio-economic group (as measured by area level deprivation using the IMD [23] and WIMD [24]. Secondary outcomes will be analysed similarly. Proposed sensitivity analyses include the investigation of missing data and the use of multiple imputation for the primary outcome. We will also investigate the effect of collection time of the primary outcome (within/without the specified time window). Pre-specified interactions of interest are age and gender with the intervention. A detailed Statistical Analysis Plan (SAP) will be completed and signed off before the database is locked and analysis begins. The trial statistician will be blind to participant allocation during analysis. Study results will be reported in line with the CONSORT statement [33].

The intervention will be delivered by three health check advisors. Any clustering by advisor in the intervention arm will be investigated via a partial cluster model of the primary outcome [34, 35]. The adjusted effect for clustering (by advisor) with 95% CI, p-value and Intra-Cluster Correlation will be reported. If the distributional assumptions for linearity are not met this analysis will use the binary primary outcome and generalized modelling.

### Qualitative Analysis

Qualitative data (observations, session recordings, participant interviews and lay advisor interviews) will be transcribed and anonymised for analysis. Thematic and content analysis will be used. Where possible, data will be triangulated and evidence derived from the process evaluation will be used to inform which aspects of the health check might make a change in relation to the outcomes. Details of the analysis to be conducted are outlined below. A Qualitative data collection and Analysis Plan (QAP) will be developed and signed off in advance of data collection and will be regularly reviewed during data collection and analysis.

#### Observations of health check sessions

Observations/audio recordings will be analysed for two main purposes. Firstly, we will ascertain fidelity by content coding anonymised transcripts of health check sessions for evidence of the BCTs identified in the health check manual [19, 36]. A fidelity definition and acceptable range will be agreed upon by the team in advance. Two researchers will be involved in coding transcripts independently and a subset will be double-coded to assess inter-rater reliability. Fidelity will be assessed using content analysis by:comparing manual-specified BCTs with the number of BCTs delivered in health check sessions;comparing delivery of BCTs according to session duration, advisor and site;examining discrepancies between health check advisors’ self-reported coverage and actual coverage of BCTs, and delivery of any BCTs that are not stipulated in the health check manual.

Secondly, we will carry out further inductive thematic analysis [37] of the audio-recorded health check sessions to gain a deeper understanding of social context and constructions of cancer awareness and help-seeking. Dual coding will be undertaken to reduce potential bias [37].

#### Interviews

Anonymised participant interview transcripts and lay advisor paired interviews will be analysed thematically [37], with 20% double coded (to ensure consistent understanding of code definitions and application between coders), to explore which aspects of the health check were perceived to be most useful, why and participants’ potential experiences of wider contextual contamination (i.e. other cancer awareness campaigns).

### Health Economic Analysis

The trial will include a health economic evaluation from an NHS perspective to provide an estimation of costs and cost-effectiveness of the health check intervention. No discounting will be applied as the length of intervention and follow-up do not exceed one year.

Implementation cost of the intervention will be calculated from resource use and standard unit costs (where available) as well as financial records. Resource use associated with the intervention will be established from site summary forms and through interviews with the lay advisors. The main components are expected to be lay advisor training, supervision and support, and advisor time and travel. As the intervention will be provided in routine health care and non-medical community support settings, we do not anticipate additional costs to the participants and will therefore not collect out-of-pocket expenses as part of the implementation cost. Healthcare resource use will be measured using an adapted Client Service Receipt Inventory to compare differences at baseline and six months.

The implementation cost will be compared to the outcomes of the trial in tabular form as part of a cost-consequences analysis that will allow comparison of costs to the main trial outcomes. We do not expect any short-term effect of the intervention on participants’ quality-of-life and will not collect these data as part of the health economic analysis. Cost-effectiveness analyses will be conducted for clinical outcomes where statistically significant differences were found. These analyses will calculate the cost per point improvement (e.g. in cancer symptom awareness, anxiety etc.) and present the results as incremental cost-effectiveness ratios. Uncertainty will be assessed using one-way deterministic and probabilistic sensitivity analyses with key parameters varied within plausible ranges (e.g. 95% CIs) and cost-effectiveness acceptability curves will be presented.

If feasible, we will develop a simple decision-analytic model to extrapolate costs and outcomes to a longer-term horizon using the intervention costs and trial outcomes. These will be supported by data available in the published literature reporting health outcomes in relation to cancer symptom awareness. Feasibility of the modelling exercise will depend on data availability in the public domain and the trial outcomes. If the trial were not to find any significant differences in the primary or secondary outcomes, modelling will be considered non-feasible. A review of the relevant literature will be conducted to inform the model. Deterministic and (if feasible) probabilistic sensitivity analyses will be conducted to account for the uncertainty in key parameters informing the analysis.

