### Aim and Objectives

The aim of the trial is to evaluate the effectiveness of a community-based cancer awareness intervention in socioeconomically deprived communities. Specific objectives are to:Test the effects of the health check on cancer symptom awareness and help-seeking behaviour among adults living in socioeconomically deprived communities in South and West Yorkshire and South-East Wales.Evaluate the costs associated with the health check and estimate the cost-effectiveness of the intervention.Assess whether the intervention was delivered as intended, whether there are any contaminating factors to understand the mechanisms of change.

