### Outcomes

The primary outcome is cancer symptom knowledge [27] including specific (e.g. rectal bleeding, unusual lump) and non-specific (e.g. tiredness, unexplained weight loss) symptoms measured at two weeks post-randomisation.

Secondary outcomes include: cancer beliefs [27]; barriers to presentation [27, 28]; help-seeking intentions [27]; state anxiety [29]; intervention implementation costs; cost-effectiveness; intentions and confidence to adopt recommended health behaviours where relevant (smoking, physical activity, weight loss, fruit and vegetable intake, alcohol consumption, screening attendance, symptom presentation) [4, 30].

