### Sample size

A sample of 246 participants is required in order to achieve 90% power to detect an effect size of 0.5 in the primary outcome of cancer symptom recognition, using a two-sided test and 5% significance threshold, and assuming 30% attrition at two weeks follow-up. An effect size of this magnitude equates to intervention participants recognising on average one extra cancer symptom during the follow-up period (SD = 2.2) [32].

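### Cost-effectiveness ratios and acceptability curves are planned only for outcomes that reach significance, with no exemption for the primary outcome

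*Protocol article*

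**What the plan says.** The second objective, under Aim and Objectives, is unconditional: "Evaluate the costs associated with the health check and estimate the cost-effectiveness of the intervention". Under Outcomes, cost-effectiveness is listed among the secondary outcomes, again without condition: "intervention implementation costs; cost-effectiveness; intentions and confidence to adopt recommended health behaviours where relevant".

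Health Economic Analysis sets out two layers of work. The first does not depend on any test: "The implementation cost will be compared to the outcomes of the trial in tabular form as part of a cost-consequences analysis". The second does: "Cost-effectiveness analyses will be conducted for clinical outcomes where statistically significant differences were found". The next sentence describes what this second layer produces: "These analyses will calculate the cost per point improvement (e.g. in cancer symptom awareness, anxiety etc.) and present the results as incremental cost-effectiveness ratios". The deterministic and probabilistic sensitivity analyses follow directly, with the statement that "cost-effectiveness acceptability curves will be presented". Read in order, the ICERs, the probabilistic analysis and the curves all belong to the conditional layer.

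The longer-term decision model has its own condition: "If the trial were not to find any significant differences in the primary or secondary outcomes, modelling will be considered non-feasible".

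**The concern.** A non-significant difference is not a zero difference. Acceptability curves show how uncertain a decision is when costs and effects are both estimated with error. A rule that produces them only after p < 0.05 removes them where the uncertainty is greatest.

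Three consequences follow.

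- A stated objective is made to depend on a p-value, and the primary outcome may end with no ICER.
- An ICER that appears only when the effect estimate is large enough to be significant has, on average, an inflated denominator, so cost per point looks too low.
- The rule covers clinical outcomes in general. An ICER could therefore be published for a secondary outcome that crossed the threshold by chance, while the primary outcome has none.

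**Working it through.** **Inputs.** From Sample size: 246 participants, 90% power, effect size 0.5, two-sided 5%, 30% attrition, SD 2.2 with one extra symptom as the target. From Randomisation: 1:1 allocation. From Main analyses: baseline symptom recognition is a covariate. The number of secondary outcomes, their independence and the baseline correlation are assumptions, marked below.

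**1. The plan's own figure.** A two-sample t-test at 0.5 SD, 90% power and two-sided 5% needs 86 per arm, so 172 evaluable. 172 / (1 − 0.30) = 245.7, rounded up to 246. The stated sample size reproduces, so 86 evaluable per arm is the planned position at two weeks.

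**2. Where the rule cuts.** Without baseline adjustment, the standard error of the standardised difference is SE = √(2/86) = 0.1525. The smallest significant difference is 1.96 × 0.1525 = 0.299 SD, or 0.299 × 2.2 = 0.66 symptoms. Take two results on either side:

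- 0.31 SD (0.68 symptoms): z = 2.03, p = 0.04. ICER and curve produced.
- 0.29 SD (0.64 symptoms): z = 1.90, p = 0.06. Neither produced.

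**3. Chance of no primary-outcome ICER, and inflation when there is one.** The chance of no ICER is the probability that |z| < 1.96 when z has mean d/SE. The mean estimate given a favourable significant result is d + SE × φ(a) / [1 − Φ(a)], with a = 1.96 − d/SE. For example, at d = 0.3, a = −0.007 and the mean is 0.3 + 0.1525 × 0.399 / 0.503 = 0.421, so the ratio is 0.421 / 0.3 = 1.40. A simulation of 2,000,000 draws per effect size gives the same results.

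| True effect (SD) | No ICER | Mean estimate if favourable and significant | Ratio to truth |
|---|---|---|---|
| 0.50 | 9% | 0.528 | 1.06 |
| 0.45 (1/2.2) | 15% | 0.497 | 1.09 |
| 0.40 | 25% | 0.465 | 1.16 |
| 0.30 | 50% | 0.421 | 1.40 |
| 0.20 | 74% | 0.391 | 1.95 |

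**4. With baseline adjustment.** The SE is multiplied by √(1 − r²), where r is the baseline to follow-up correlation. The article does not give r; 0.5 and 0.7 are assumed.

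| True effect (SD) | No ICER, r = 0.5 / 0.7 | Ratio to truth, r = 0.5 / 0.7 |
|---|---|---|
| 0.50 | 3% / under 1% | 1.02 / 1.00 |
| 0.30 | 38% / 21% | 1.27 / 1.13 |
| 0.20 | 67% / 55% | 1.73 / 1.48 |

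**5. Chance secondary results.** Counting the Outcomes list gives four scales (beliefs, barriers, help-seeking intentions, anxiety) and seven behaviours, so 11. If there is no true effect on any of them, they are independent, and each is tested at two-sided 5%, the chance that at least one is significant in the favourable direction is 1 − 0.975¹¹ = 24%.

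**The case against.** The strongest reply is that the economic evaluation survives a non-significant result. The costs half of the objective is never conditional, the cost-consequences table is produced regardless, and Main analyses reports the primary effect with a 95% confidence interval whatever its p-value. A reader could divide one by the other. This stands, and it rules out a tempting inference that the objective would go wholly unanswered. What would be missing is the joint uncertainty of cost and effect and the acceptability curve, which the table is not described as giving.

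A reader might also infer that the published cost per point would be about half the truth. That needs a true effect of 0.2 SD and no baseline adjustment, where a favourable significant primary result occurs only about 26% of the time. At the planned 0.5 SD the inflation is small.

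A false-positive chance of 43% (1 − 0.95¹¹), or 60% for 18 outcomes if intention and confidence are counted separately, is equally tempting. Those figures include results in the harmful direction. The favourable-only values are 24% and 37%. Both assume independence, which is doubtful for intention and confidence about the same behaviour, and the article does not say which measures count as clinical outcomes. Nor does its silence on multiplicity show that none is planned, since a detailed SAP is promised before database lock.

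Finally, the condition on the decision model applies only if no primary or secondary outcome differs significantly. Declining to extrapolate from a trial with no significant finding is a resource choice declared in advance, not an error.

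**Conclusion.** The point holds. It rests on a rule that the article states, not on something left to another document. The rule conflicts with an objective and a listed outcome that carry no such condition, and it drops the uncertainty analysis where it is most informative.

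Its size depends on the true effect. Without baseline adjustment, the primary outcome would lack an ICER and curve about 9% of the time at the planned 0.5 SD, 15% at the one-symptom difference (0.45 SD) and 50% at 0.3 SD. The inflation factors of 1.40 and 1.95 are upper values that fall with baseline adjustment. The 24% for secondary outcomes depends on the assumed count and on independence.

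The primary comparison, sample size and data collection are untouched, and the problem can still be put right at the analysis stage. It should be fixed, but the trial's main result does not depend on it.

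**What to change.** Replace the conditional sentence under Health Economic Analysis with wording to this effect: incremental cost, incremental effect, the ICER with its planned probabilistic analysis, and the acceptability curve will be reported for the primary outcome whatever its p-value. Any ICERs for secondary outcomes will be for outcomes named in advance, not chosen by significance.

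The cost-consequences table and the planned sensitivity methods can stay as they are. So can the condition on the decision model.

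The cost is a change of wording in the protocol and the economic analysis plan and, if the primary result is not significant, one extra ICER and curve from data already being collected.

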### Ethics

This trial has been assessed as low risk. No adverse events are being collected due to the short contact period with each participant and the potential for this to create unnecessary burden on participants. Informed consent is taken from each participant at recruitment. Where a participant has not consented to take part in a qualitative interview, intervention delivery audio recording or observation they will not be approached regarding these aspects of the trial.

Some participants may find it difficult to talk about cancer, may find questions about cancer symptoms uncomfortable to discuss or may feel embarrassed about their lifestyle. When dealing with participants, researchers will be mindful that questions could be upsetting and that the social determinants of health, including the person’s environment, are important drivers of behaviour [38] alongside self and societal stigma relating to obesity, smoking and alcohol use [39, 40].

Research staff are experienced in collecting sensitive data and specific training is provided to support staff. In order to provide participants with privacy to discuss their responses with the lay advisor, the baseline assessments take place in a private room. Participants are reminded that their participation is highly confidential and any information they share will not be shared with other parties. Follow-up phone assessments are scheduled at a time suitable to participants which allows them to find a private space to talk. However, if at any point any participant becomes upset they are provided with support and, where appropriate, additional support services are highlighted to them. Participants are additionally offered a break and/or are able to continue their participation at a different date/time if they wish.

Research data will be held for 15 years and archived securely. This is in line with Cardiff University policies.

### Dissemination

Study results will be disseminated widely through academic, clinical, policy and community networks and to trial participants. An inclusive publication policy has been developed to support this and provides all members of the team with an opportunity to volunteer ideas and input to planned outputs. The publication policy will be discussed at monthly meetings and any new ideas added.

## Disscussion

This is the first randomised controlled trial of a facilitated behaviour change intervention aimed at improving cancer awareness in socioeconomically deprived communities in the UK. Previous research suggests that tailored community-based interventions delivered by trusted lay advisors could lead to an increase in cancer symptom awareness and encourage help-seeking behaviour among adults living in disadvantaged communities, for whom long-term health may not be a priority due to competing life demands and low socioeconomic resources [39]. High quality evidence is needed to test the effectiveness of such interventions within real life settings. The current trial follows on from theory modelling [19] and feasibility testing [16], according to the MRC guidance on developing and evaluating complex interventions [22]. We aim to reach individuals in deprived areas who experience the poorest long-term cancer outcomes. However, despite broad inclusion criteria, the trial excludes individuals who lack capacity to provide informed consent and those who do not speak English, who may have the highest need. In addition, it is not designed to reach members of the community who do not or who are unable to (e.g. people who are housebound) attend the community venues that are targeted within this trial. Arguably, these populations may have higher needs and may be even harder to reach and engage [41]. Future research could consider how to extend reach to these populations within disadvantaged communities.

## Conclusion

The findings of the trial will be critical to informing effective methods of engaging high risk disadvantaged populations in cancer awareness, with the potential to reduce socioeconomic inequalities in cancer outcomes and the possibility of wider implementation across the UK.

## Abbreviations

ABACus: Awareness and Beliefs About Cancer trial
ABC: Awareness and Beliefs about Cancer measure
BCT: Behaviour Change Techniques
CI: Confidence Intervals
CONSORT: CONsolidated Standards Of Reporting Trials
GDPR: General Data Protection Regulation
GP: General Practitioner
HCA: Health Check Advisor (lay advisor)
IMD: Index of Multiple Deprivation
ISRCTN: International Standard Randomised Controlled Trial Number
MRC: Medical Research Council
NHS: National Health Service
QAP: Qualitative data collection and Analysis Plan
SAP: Statistical Analysis Plan
SD: Standard Deviations
SPIRIT: Standard Protocol Items: Recommendations for Interventional Trials
STAI-6: Six-item short-form State-Trait Anxiety Inventory
WIMD: Welsh Index of Multiple Deprivation
